### Exposure and control

We will divide the participants into two groups according to whether they have dyslipidemia, which means that dyslipidemia is an exposure factor in this study.

### Outcomes of interest

The pre-specified outcomes will be observed in detail and the outcomes reflecting bone transition are described. The primary outcome is the incidence of OP. During the study period, the condition of normal bone mass, osteopenia, and fragility fracture for each female will be also identified every year. For the event of OP-related fracture, different sites, occurrence times, and the number of fractures are completely recorded.

The secondary outcomes are radiographic BMD assessment and serum marker test. The blood indexes aim to reveal the dynamic changes in calcium and phosphorus metabolism, osteogenesis, and osteoclast function. Also, the recognized scales such as the health question scale, and specific relevant TCM syndrome differentiation scale will be investigated.

### Questionnaire information

Face-to-face structured interviews will be done with a well-designed questionnaire by trained interviewers. The questionnaire will be used to collect information on the five collected domains. The aspects include: (1) general demographic information; (2) lifestyle and dietary behavior; (3) health status, comorbidities, and medication-taking condition; (4) recognized scales measuring osteoporosis risk, physical activity or quality of life; and (5) characteristics of TCM syndromes.

All the subjects with the researchers will complete the questionnaires at baseline and follow-up phase. Then, a complete post-enumeration check of the questionnaires will be performed.

### BMD measurement

The BMD values can be measured at multiple skeletal sites using the accepted dual-energy x-ray absorptiometry (DXA) scanner manufactured by Hologic Inc. In the absolute BMD measurement of the human body, it is necessary to record the information of the lumbar spine, both hips, and the distal one-third of the radius site. In addition, the total *T-*value and the *T-*value of each site will be reported separately. Definitions of osteopenia and OP are in accordance with WHO standards on BMD measurement.

### Laboratory test

Each participant will be required to complete blood specimen collection in the fasting state. In total 10 ml of blood sampling will be collected through intravenous vacuum blood method after a nurse checks the personal information. Then the samples will be centrifuged and cryopreserved according to the standard operating procedures.

The indicators will include serum alkaline phosphatase, osteocalcin, bone-specific alkaline phosphatase, serum type I procollagen C-terminal peptide, serum type I procollagen N-terminal peptide, and 25OHD. Biochemical indicators such as liver and kidney function, plasma glucose, total cholesterol, triglycerides, high-density lipoprotein, low-density lipoprotein, and uric acid will be also tested. Meanwhile, the BMD measurement and laboratory tests annually will be cost-free in the process of study.

The Guangzhou KingMed Diagnostics Limited Liability Company will be responsible for collecting, transporting, and testing blood samples. Samples that cannot be sent in time for testing will always be stored in a 4°C refrigerator (within 6 h); if the sample cannot be sent on the day of collection, the serum will be centrifuged (centrifugation conditions: 2,500 ~ 3,000 rpm, 4°C, 5 min) and retained and frozen in a −20°C refrigerator until sent for testing. Blood samples will be kept at −20°C during all transport processes.

### Follow-up program

All of the participants will be followed up by face-to-face interviews as far as possible. In the follow-up survey, we will conduct in the same way as the baseline investigation. For mobility-impaired fracture patients in some cases, a survey with options for telephone interview may be considered.

First, the detailed information on the telephone number of the subject or their relatives and clear home address will be noted down. Second, the researcher in-charge will contact the participants ahead of time on both workdays and weekends to ensure they can participate in the follow-up every year. Third, the self-reported disease status and medication use will be collected through telephone interviews or household surveys when the on-site follow-up is not available. For the subjects who could not be investigated face-to-face or contacted by telephone surveys, medical records in designated hospitals or community healthcare centers will be acquired possibly to confirm their health status. The expected proportion of participants lost to follow-up is below 10%.

### Sample size calculation

We calculated that a minimum sample size of 1,100 (550 DL and 550 non-DL) women are required to demonstrate an 8% difference in the prevalence of OP between DL and non-DL participants (14). The assumes are as follows: best-estimate OP prevalence of 12% among non-DL women and 20% among DL women; 5% level of significance; 90% power for a two-sided test. Furthermore, we considered a 20% dropout rate and finally calculated the sample size.

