### Participants

Due to the potential impact of different socioeconomic conditions on population bone mass, participants in this study will be recruited in different regions of mainland China (namely, northern China, southern China, and central China) from October 2022 to May 2023. The aim is to avoid the potential bias caused by economic circumstances, education, work, and other factors.

The subjects will be enrolled according to the established eligibility criteria: (1) Post-menopausal women; (2) aged from 45 to 64 years old; (3) *T-*value of bone density measurement is >-2.5; and (4) the participants are willing to participate in the investigation study.

Restrictive exclusion criteria are defined as follows: (1) A fragility fracture is found in the enrolled female; (2) the population who suffers from mental illness or are unable to complete the study.

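### The 90% power is stated for a difference in OP prevalence, but the cohort enters free of OP and its primary outcome is incidence, so the power of the primary comparison is conditional on incidences that the article does not state

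*Protocol article*

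**What the plan says.** All references are to the protocol article.

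- Sample size calculation: the target is to "demonstrate an 8% difference in the prevalence of OP between DL and non-DL participants". The inputs are "best-estimate OP prevalence of 12% among non-DL women and 20% among DL women", with "5% level of significance; 90% power for a two-sided test". The result is a "minimum sample size of 1,100 (550 DL and 550 non-DL) women are required", and the section adds that "we considered a 20% dropout rate and finally calculated the sample size".
- Participants: one entry criterion is that the T-"value of bone density measurement is >-2.5". A fragility fracture is an exclusion.
- BMD measurement: OP is defined by the WHO standards for BMD.
- Outcomes of interest: "The primary outcome is the incidence of OP".
- Study design and settings: annual visits for a minimum of 3 years, to follow the occurrence of OP.
- Statistical analysis: the incidence of OP is counted in each group.
- Follow-up program: loss to follow-up is expected to be below 10%.

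**The concern.** Prevalence is the share of women who have OP at a point in time. Incidence is the share of women without OP who develop it over a period. The entry criteria set BMD-defined OP to zero in both groups at baseline, so whatever OP the study observes must arise during follow-up. The calculation names prevalence both for the difference it targets and for its two inputs. No section gives an expected incidence, ties 12% and 20% to a length of follow-up, or converts them.

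The 90% power is the only quantitative support for 1,100 women. If new OP turns out rarer than 12% and 20%, a null result could be reported as coming from a study with 90% power when that power was never established for the outcome analysed.

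**Working it through.** **Inputs from the article.** Proportions 0.12 and 0.20; two-sided alpha 0.05 (z = 1.960); power 0.90 (z = 1.2816); equal groups; 20% dropout; expected loss below 10%; minimum follow-up 3 years.

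**1. Reproducing the stated figure.** Two proportions, pooled variance under the null, mean proportion p̄ = 0.16:

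n = [1.960·√(2·0.16·0.84) + 1.2816·√(0.12·0.88 + 0.20·0.80)]² / 0.08² = (1.0162 + 0.6605)² / 0.0064 = 439.2, so 440 per group.

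440 / (1 − 0.20) = 550 per group, 1,100 in total. This matches exactly, and power at 440 per group is 90.0%.

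**2. What the inputs mean as incidence.** If 12% and 20% are 3-year cumulative risks at a constant hazard:

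- non-DL: −ln(0.88)/3 = 0.043 per year
- DL: −ln(0.80)/3 = 0.074 per year

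No section gives or supports these rates for women aged 45 to 64 who enter without OP.

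**3. Power if incidence is lower.** The article gives no incidence, so the non-DL risk is varied as an assumption. Evaluable women per group are 550 × 0.80 = 440 (the planned dropout) or 550 × 0.90 = 495 (10% loss).

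Power = Φ{[Δ√n − 1.960·√(2p̄(1−p̄))] / √(p₁(1−p₁) + p₂(1−p₂))}

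Example, 6% vs 10%, n = 440: (0.04·√440 − 1.960·√(2·0.08·0.92)) / √(0.06·0.94 + 0.10·0.90) = (0.8390 − 0.7520)/0.3826 = 0.227, and Φ(0.227) = 59%.

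Keeping the ratio 20/12 = 1.67:

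| non-DL vs DL risk | 440 per group | 495 per group |
|---|---|---|
| 12% vs 20% | 90% | 93% |
| 10% vs 16.7% | 83% | 87% |
| 8% vs 13.3% | 73% | 78% |
| 6% vs 10% | 59% | 64% |
| 4% vs 6.7% | 42% | 46% |

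Keeping the absolute difference of 8 points instead, the same formula gives 98% at 6% vs 14% with 440 per group. Power rises on this scale because the variance shrinks while the difference stays fixed.

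**4. Detectable DL risk.** Solving the power formula for 90% with 440 per group: a non-DL risk of 6% needs 12.3% in DL women (risk ratio 2.05), and a non-DL risk of 4% needs 9.5% (risk ratio 2.37).

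**The case against.** The strongest reply is that prevalence is loose wording. In a cohort with no OP at entry, the proportion with OP at the end of follow-up is close to the cumulative incidence, and on that reading 1,100 stands. The two percentages are linked to a cited source that could not be consulted, so the text does not establish that they are point prevalences from an unselected population. This reply is plausible, and it limits what can be claimed. It does not settle the matter: the article uses incidence for its outcome and prevalence for its sizing, and even on the generous reading the follow-up period and the basis for the two risks are missing.

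Three further points stand in part.

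- Follow-up is a minimum of 3 years. A longer horizon would raise cumulative incidence, but the article commits to no longer one.
- The allowance for 20% dropout is generous against an expected loss below 10%. With 495 per group the power at 6% vs 10% is still 64%.
- The target is stated as an absolute difference, not a ratio. Holding 8 points fixed, power goes up at lower risks. The choice of scale is an assumption either way.

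A reader might go further and infer that real power is around 40% to 60%. The documents do not support that. A model of bone loss that gives both groups the same rate of loss would yield low power, but it assumes away any effect of DL on loss during follow-up, which is what the cohort is meant to study. Extrapolating from the Introduction's 51.6% OP prevalence applies a figure for women over 65 to a cohort aged 45 to 64, over an interval that has to be guessed.

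**Conclusion.** The point holds as a mismatch between the quantity powered and the primary outcome. It should be fixed. It is not an arithmetic error, since the stated sample size reproduces exactly. The mismatch follows from the text alone. Its effect on power does not: 90% applies to incidence only if the cumulative risks reach 12% and 20%; it falls to between 83% and 42% over non-DL risks of 10% down to 4% if the ratio of 1.67 is kept (440 per group); and it does not fall if the 8-point difference is kept. The power for the primary outcome is therefore unknown. With 1,100 unchanged and no change to conduct or analysis, this is a correction to the justification, not a reason to doubt the design.

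**What to change.** Keep 1,100 and rewrite only the Sample size calculation section:

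- Express the two rates as cumulative incidence of OP, over a stated follow-up period, in women free of OP at baseline, and give the basis for each.
- State that 90% power is conditional on 12% vs 20%.
- Add a short table of the DL risk detectable with 90% power at lower non-DL risks (at 440 per group: 12.3% when non-DL is 6%; 9.5% when it is 4%).

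The Introduction's uses of prevalence are correct and should stay. The cost is wording and a small table. No participants are added; the stated power becomes conditional.

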### Data management

The stepwise data management process is designed for implementation in this study. The electronic data will be input by the two independent assistants through the Epidata database. All the information will be confirmed eventually after the consistency check of the data are completed. During the follow-up period, clinical data management will be developed based on the needs of predetermined outcome research, including the main outcome measure and updated examination results.

### Statistical analysis

Statistical analyses were conducted by using SAS 9.4 (SAS Institute, Cary, NC) and R software 4.1.1 (R Foundation for Statistical Computing, Vienna, Austria). Figures were created in GraphPad Prism 8.0 (GraphPad Software, CA, USA). The continuous variables which are in accord with normal distribution will be expressed as the mean and standard deviation, while the measurement data that do not coincide with normal distribution will be expressed as the median and interquartile range. In the description analysis, the *t-*test or the Mann–Whitney *U*-test will be used for comparing quantitative data between the two groups. On the contrary, the count data will be presented as frequency and percentage, and the χ^2^-test will be applied for the comparison between the two groups.

The incidence of OP in two groups will be counted. Generalized estimation equations will also be designed to confirm the effect of potential risk factors on OP. A non-adjusted model and a multivariate-adjusted model will be utilized, and the results will be reported using unadjusted, minimally adjusted, and fully adjusted analysis, according to the specifications of the STROBE statement. A two-sided *alpha* of 0.05 will be considered to be statistically significant.

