## Methods

### Study design and settings

The multicenter, prospective cohort study aims to explore the clinical associations between the DL and OP in Chinese postmenopausal women. Data will be collected from a representative sample and the participants will be recruited from multiple hospitals and communities in China. Then, the subjects will be divided into two groups according to whether there is dyslipidemia or not, and an epidemiological investigation will be conducted.

Each participant will be visited continuously once every year with a minimum follow-up of 3 years to track incidences of OP. Furthermore, BMD screening and biological samples will also be gathered. The questionnaire will be administered to collect information about personal characteristics such as health status and potential risks. Important information including the incidence of OP and/or fracture and medication use will be confirmed annually during the follow-up period. The required sample size will be at least 1,100 patients based on a power analysis. A flow chart of the research process is shown in Figure 1.

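### The primary outcome is incidence of OP, but the analysis named for it (a count, a chi-square test and GEE on OP) makes no use of time at risk or censoring

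*Protocol article*

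**What the plan says.** All references are to the protocol article.

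- **Outcome.** Outcomes of interest: "The primary outcome is the incidence of OP". The bone-density entry criterion under Participants, which refers to the T-value, is "value of bone density measurement is >-2.5", and women with a fragility fracture are excluded. The event is therefore first onset.
- **Follow-up.** Study design and settings: "Each participant will be visited continuously once every year with a minimum follow-up of 3 years to track incidences of OP". No common end of follow-up and no analysis time point is given.
- **Yearly status.** Outcomes of interest: "During the study period, the condition of normal bone mass, osteopenia, and fragility fracture for each female will be also identified every year". Medication use is also recorded each year (Study design and settings).
- **Loss.** Follow-up program expects loss below 10%. Sample size calculation says "we considered a 20% dropout rate and finally calculated the sample size".
- **Analysis.** Statistical analysis: "The incidence of OP in two groups will be counted". Count data are compared by a chi-square test. Then: "Generalized estimation equations will also be designed to confirm the effect of potential risk factors on OP", with unadjusted, minimally adjusted and fully adjusted results.

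**The concern.** Incidence needs a risk set and either a fixed horizon or person-time. The section names neither.

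A count has no definite meaning until its denominator and time point are fixed. A GEE fitted to OP status at every annual visit would count a converted woman again each later year. If her T-value later rose above the threshold, she would return as a non-case. Such a model describes how common OP is across visits, not how often it newly occurs.

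At stake are the headline incidence figures and, under some patterns of loss or treatment, the DL effect itself. The Discussion hopes to shed light on a potential causal relationship, so the main estimate should match the stated outcome.

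**Working it through.** **1. The plan's own figure.** Inputs from Sample size calculation: 12% vs 20%, two-sided 5%, 90% power, 20% dropout. With pooled variance (mean proportion 0.16):

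n = [1.960·√(2·0.16·0.84) + 1.282·√(0.12·0.88 + 0.20·0.80)]² / 0.08² ≈ 440 per group; 440/0.80 = 550 per group, 1,100 in total.

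This reproduces the stated number exactly. It is a comparison of two proportions at one fixed time, and that section calls the proportions prevalence without a horizon.

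**2. Assumption.** Read 12% and 20% as 3-year risks. The yearly conversion probability is q = 1 − (1 − p)^(1/3): 0.0417 for non-DL and 0.0717 for DL. The hazards are −ln(0.88)/3 = 0.0426 and −ln(0.80)/3 = 0.0744, a hazard ratio of 1.75.

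**3. Count over enrolled women.** With total loss d by year 3, spread evenly and unrelated to OP, yearly retention is s = (1 − d)^(1/3). The observed count per enrolled woman is sq + s²(1−q)q + s³(1−q)²q. The enrolled denominator is an assumption.

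| Loss non-DL / DL | Non-DL | DL | Risk ratio | Difference (points) |
|---|---|---|---|---|
| none | 12.0% | 20.0% | 1.67 | 8.0 |
| 10% / 10% | 11.2% | 18.7% | 1.67 | 7.5 |
| 20% / 20% | 10.4% | 17.3% | 1.67 | 6.9 |
| 10% / 30% | 11.2% | 15.9% | 1.42 | 4.7 |
| 20% / 5% | 10.4% | 19.3% | 1.86 | 9.0 |

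Equal loss lowers both risks and leaves the ratio alone. Unequal loss moves the ratio. The 30% is an assumption above either figure in the article.

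**4. Length of follow-up.** The same hazards at 5 years give 1 − 0.88^(5/3) = 19.2% and 1 − 0.80^(5/3) = 31.1%.

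**5. GEE on yearly status, if that is the response.** With no reversal, prevalence at visits 1, 2 and 3 is 4.2%, 8.2%, 12.0% (non-DL) and 7.2%, 13.8%, 20.0% (DL). The visit averages are 8.1% and 13.7%. Reversal rates below are assumptions; the article gives none.

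| Yearly reversal | Non-DL | DL | Difference (points) | Odds ratio |
|---|---|---|---|---|
| 0% in both | 8.1% | 13.7% | 5.6 | 1.79 |
| 20% in both | 7.1% | 11.9% | 4.8 | 1.78 |
| 40% in both | 6.2% | 10.4% | 4.2 | 1.76 |
| 20% non-DL, 40% DL | 7.1% | 10.4% | 3.3 | 1.52 |

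Equal reversal shrinks the absolute figures but hardly touches the odds ratio. Unequal reversal does change it.

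**6. Unequal loss under GEE.** With 10% vs 30% loss and no reversal, the odds ratio pooled over attended visits is 1.74 against 1.79 without loss, and the visit-specific odds ratios do not change. Loss that depends on DL status alone therefore distorts the count far more than the GEE.

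**The case against.** The strongest reply is that the criticised model is assumed. The article states no response, link or risk set for the GEE. A GEE on visits up to first OP with a complementary log-log link would be essentially the hazard model proposed below. Such detail is often left to a fuller document. Counting and GEE are also separate steps, and the GEE is introduced for risk factors rather than as the estimator of incidence. A count at a fixed year-3 visit among women followed to that visit is a valid incidence proportion if loss is non-informative. Recruitment runs only from October 2022 to May 2023, so planned follow-up differs between women by months at most.

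Much of this stands, and it rules out three stronger readings that a reader might infer:

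- *That the plan cannot estimate incidence.* The text is compatible with versions of the count and the GEE that would.
- *That unweighted GEE is valid only if dropout is completely at random.* Dropout may depend on covariates in the model, and DL would be one of them.
- *That the DL effect is biased.* With equal reversal the odds ratio hardly moves, and loss depending on DL alone barely affects the GEE (step 6).

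What the reply does not remove is the mismatch in what is written. The outcome is first onset over time with loss expected, and the methods named are ones that, taken at face value, ignore time at risk. The sample size section's use of prevalence for the same quantity makes the yearly-status reading more plausible.

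**Conclusion.** The concern holds as a mismatch between the primary outcome and the analysis named for it.

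Its certain part is that no horizon, denominator or censoring enters the stated analysis. On the assumption that 12% and 20% are 3-year risks, that leaves room for reported figures as far apart as 10.4% vs 17.3% (enrolled denominator, 20% loss in both groups), 19.2% vs 31.1% (5 years) and 8.1% vs 13.7% (visit average).

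Its conditional part is the DL effect. The relative effect is little changed when loss and reversal are equal across groups (odds ratio about 1.76-1.79 against a hazard ratio of 1.75). It shifts if reversal after diagnosis differs by group or, in the count, if loss does: a risk ratio of 1.42 instead of 1.67 with 10% vs 30% loss. The horizon, denominator, reversal rates and unequal losses are illustrative assumptions, not figures from the article. The change is worth making before analysis; it does not call the design or the sample size into question.

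**What to change.** - **Primary analysis.** Use a discrete-time hazard model with complementary log-log link on at-risk visits, from baseline to the first DXA showing OP. Treat OP as absorbing and censor at the last DXA.
- **Reporting.** Give life-table cumulative incidence at 3 years per group, with the difference and its confidence interval. Keep the three levels of adjustment already planned.
- **GEE.** Keep it, or a mixed model, for repeated BMD and serum markers.

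**Cost.** Revised wording, slightly more analysis work, and a standard model in the SAS or R already named. No new data are needed.

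No more women are needed either. At a hazard ratio of 1.75, Schoenfeld's formula asks for 136 events for 90% power. With 440 per group retained, 440·(0.12 + 0.20) ≈ 141 events are expected, giving about 91% power; with 10% loss it is about 158 events and 94%.

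**Limit.** Censoring must still be non-informative given the covariates. Follow-up program foresees telephone interviews for some mobility-impaired fracture patients, so missed scans may be related to bone status. Reasons for missing DXA should be reported by group.
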